##### LLD

- Type of the LLD(s) prescribed.

- Doses of the LLD(s) prescribed.

#### Number of laboratory tests of LDL-C

- Number of laboratory tests of LDL-C performed before (in 2009), during (2010-2011) and after the intervention (in 2012) in patients with an IHD diagnosis.

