### Study period

The study will be undertaken between January 2009 and January 2012.

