#### a) Presential training sessions and interactive workshops

Doctors from the 11 primary care centres and the two hospital services (Cardiology and Internal Medicine) will be informed about the CPG and the various measures of secondary coronary heart disease prevention (how to achieve the target levels of LDL-C). Two doctors (one from primary care and the other from a hospital), previously trained by the research team, will lead the sessions that will take place in each primary care centre and hospital service. Two types of session will be held:

- An initial two-hour training session.

- A one-hour refresher session, a year after the initial training session, where the initial results will be presented and attendees will be reminded of the key points.

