### Forecast execution dates

The project will be carried out over three years.

September 2009: presentation of training material, standardized training for trainers.

January 2010: classroom and face-to-face satisfaction survey.

March 2010-June 2010: on-line course.

January 2011-March 2011: post-intervention analysis of results.

May 2011 Feed-back and reminder of GPC.

January 2012-September 2012: data processing, statistical analysis, data interpretation, preparation and dissemination of results.

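### The 2012 'after' window for LDL-C test counts lies almost wholly outside the study period and is not comparable with 2009, and the 2011 'post-intervention' analysis precedes the feedback component

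*Protocol article*

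**What the plan says.** All references are to the protocol article.

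- **Number of laboratory tests of LDL-C** defines a secondary variable, the number of tests "performed before (in 2009), during (2010-2011) and after the intervention (in 2012").
- **Measurements** says that the number of tests per patient before and after the intervention will inform the judgement of how well patients are controlled.
- **Study period**: "The study will be undertaken between January 2009 and January 2012".
- **Forecast execution dates** puts the classroom session in January 2010 and the on-line course in March to June 2010. The next entry reads "January 2011-March 2011: post-intervention analysis of results". Feedback and the guideline reminder are then set for May 2011, and the calendar closes with "January 2012-September 2012: data processing, statistical analysis, data interpretation, preparation and dissemination of results".
- **Intervention** makes personal feedback, about a year after the first training, part of the intervention. **Presential training sessions and interactive workshops** adds "A one-hour refresher session, a year after the initial training session", at which initial results are shown.
- **Main independent variable** takes the baseline LDL-C status from the last value recorded during 2008. **Analytical strategy** compares control at baseline with control at study end by the McNemar test and gives no calendar dates for the end value.

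**The concern.** In an uncontrolled before-and-after study the time windows are the comparison; there is no parallel group to absorb an error in them. Here the dates for one variable conflict with the dates for the study as a whole.

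Two things are at stake. First, the test count is meant to help interpret LDL-C control. If the 'after' count is cut short by the calendar, it will show a fall in testing that reflects only the length of the window. Second, an analysis called post-intervention is dated before the last component is delivered. If it were later used as the after-measurement, it would describe the effect of the initial training and on-line course without the feedback.

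**Working it through.** The plan states no figure for this point, so the check is a count of calendar months.

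**Inputs.** Study period: January 2009 to January 2012. Test windows: 2009, 2010-2011 and 2012. Analysis phase: January to September 2012. Classroom session: January 2010. Early analysis: January to March 2011. Feedback: May 2011.

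**Step 1: where the 2012 window falls.**

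| Part of 2012 | Months |
|---|---|
| Inside the study period (January) | 1 |
| After the study period (February-December) | 12 − 1 = 11 |
| Coinciding with analysis and dissemination (January-September) | 9 |
| After the last scheduled activity (October-December) | 12 − 9 = 3 |

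**Step 2: effect of window length.** At a constant testing rate r per month, the expected count is r × months, so r cancels in the ratio to 2009.

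| Window | Months | Ratio to 2009 | Apparent change |
|---|---|---|---|
| 2009 | 12 | 1.00 | reference |
| 2010-2011 | 24 | 24/12 = 2.00 | +100% |
| 2012, cut at the end of the study period | 1 | 1/12 = 0.083 | −92% |
| 2012, cut at the end of the analysis phase | 9 | 9/12 = 0.75 | −25% |
| 2012, full year | 12 | 12/12 = 1.00 | 0% |

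Only the last row is comparable with 2009, and it needs data from months that come after every activity in the calendar.

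**Step 3: order of analysis and feedback.** The early analysis ends in March 2011 and feedback is in May 2011, 2 months later. It cannot describe the state after all components.

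**Step 4: time left after the feedback.** May 2011 to January 2012 is 8 months, inside the study period. June to December 2011, 7 of those months, carry the label 'during' in the test-count variable although no component remains to be delivered.

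**Step 5: the starting point.** The baseline for LDL-C control is 2008, but the 'before' year for test numbers is 2009. Tests from 2009 therefore do not describe how intensively patients were monitored when their baseline status was set.

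**The case against.** **Only a secondary count is dated to 2012.** This stands. A reader might infer that the end-of-study LDL-C must also come from 2012, hence from January 2012 alone, so that most patients would lack a paired value. No section says so. The baseline rule takes the last value over a whole year, and the same approach at study end would use values up to January 2012. Eight months after the feedback are available.

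**An analysis before the feedback is needed.** This also stands. The refresher is to present initial results, so results must exist by then, and the calendar schedules the statistical analysis separately in 2012. A reader might take the order of events as a design fault; it is not. The fault is the label.

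**The article does not say that raw counts will be compared.** True: no analysis is specified for this variable, and rates or offsets could sit in the full analysis plan. But the windows themselves are stated, and they conflict with other stated dates. An analysis plan can convert counts to rates; it cannot supply months that the schedule does not collect.

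**Forecast dates are approximate.** Fair, and for this reason little weight belongs on the interval of 16 months between the January 2010 session and the feedback, against the stated year. Counted from the on-line course it is 11 to 14 months. Approximation does not explain 11 months outside the study period, however. The Study period section and the calendar agree with each other that analysis starts as the study closes; the test-count section is the one out of line.

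**Conclusion.** The dates conflict and need correction. As written, 11 of the 12 'after' months for LDL-C test numbers lie outside the study period, 9 of the 12 overlap the analysis and dissemination phase, and a full-year count to set against 2009 cannot be obtained. If the count is cut at the end of the study period, window length alone gives a fall of about 92%; if cut at the end of the analysis phase, 25%. These percentages assume a constant testing rate and a comparison of unadjusted numbers; they do not depend on the value of the rate.

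The January to March 2011 analysis is an interim look and cannot be the final after-measurement.

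The documents do not support the conclusion that the primary outcome is unmeasurable. It can be measured after the feedback and before the study closes, and the plan should say that it will be. The point deserves correction before data extraction, but it does not undermine the main comparison.

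**What to change.** 1. Reconcile Study period, Main independent variable (baseline 2008), Number of laboratory tests of LDL-C ('before' 2009) and Forecast execution dates, so that one set of dates defines before, during and after for both the LDL-C outcome and the test count.
2. Choose one of two routes for 'after': (a) extend the e-cap extraction through December 2012 and move the analysis; or (b) redefine 'after' to start once the May 2011 feedback is delivered and to end with the study in January 2012, closing the 'during' window at the feedback.
3. Analyse test numbers as rates per patient-year, with each patient's observed time as the offset, or over windows of equal length. Rates also handle patients newly diagnosed in 2009-2010, who contribute only part of a window.
4. Define the end-of-study LDL-C as the most recent value after the feedback.
5. Rename the January-March 2011 analysis *interim results for feedback*.

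The data are routine records, so no visits or tests are added. Route (b) costs text edits and a rate analysis. Its drawback is a window of about eight months against a full-year baseline, so more patients may have no end value, and their number should be reported. Route (a) gives a full year but delays the analysis by some months.

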#### Assessment of professional participation

- Number of physicians who have attended the presential (classroom) session.

- Number of physicians who have undertaken the on-line course.

#### Sociodemographic characteristics of physicians

- Hospital or primary care physician, gender, age, employment status (steady or locum), specialist by residency training system or not, Catalan Health Institute referral hospital or not, teaching unit, assistance quality standards and drug prescription standard.

#### Characteristics of Primary Care Centres

Drug prescription quality standard, assistance quality standards, assigned population, attended population, number of patients by doctor, teaching or non-teaching primary attention centre, rural or urban location, and referral hospital status.

### Statistical analysis

#### 1. Sample size

At present, the percentage of good control of LDL-C levels of patients with IHD in our area is around 35% (assistance quality standards results for our area calculated from the primary care information services of Catalonia Institute of Health). Considering this value as a starting point, we estimate that it would be reasonable to expect an increase in control efficiency of at least 10% following this intervention.

We assume an average of 25 patients per physician with a 95% confidence interval (CI) of 0.05. Accepting an alpha error of 0.05 and 90% statistical power for bilateral contrasts and assuming a 20% loss rate, would require an estimated sample size of 2,761 patients. To achieve this sample, given a 2.4% prevalence of IHD in our population of 142,549 adult inhabitants, 115,042 health service users will be needed.

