## Methods/Design

### Study design

The design is a quasi-experimental uncontrolled before-and-after study, investigating patients seen by physicians in primary care centres and hospitals in the Terres de l'Ebre region covered by the Catalan Institute of Health.

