#### 2. Analytical strategy

The statistical analysis will be preceded by an examination of outliers, data cleaning, identification and labelling of missing and/or unenforceable values, and labelling of variables and variable categories.

Variables will be summarised as the mean and 95% CI for continuous variables, and as absolute values or percentages and 95% CI for categorical variables. Statistical significance will be concluded for values of p < 0.05. The difference in percentage control of LDL-C levels between baseline and the end of the study will be assessed using the McNemar test. To assess the improvement of control of c-LDL an analysis of covariance using logistic regression will be carried out. Subsequently, a multilevel logistic regression model will be developed. The main independent variable in the both models will be "intervention", adjusted for baseline values and potential confounders. Physician will be considered a cluster in the multilevel regression).

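### The sample size of 2,761 and its 90% power belong to a comparison of two independent groups, not to the single before-after cohort tested with McNemar; the error is conservative and needs a reporting correction

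*Protocol article*

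**What the plan says.** All of these statements are in the protocol article.

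- **Statistical analysis, 1. Sample size.** The baseline is given by "the percentage of good control of LDL-C levels of patients with IHD in our area is around 35" per cent, and the expected effect is "an increase in control efficiency of at least 10% following this intervention". The clustering input reads "We assume an average of 25 patients per physician with a 95% confidence interval (CI) of 0.05". The error rates are set by "Accepting an alpha error of 0.05 and 90% statistical power for bilateral contrasts", and a 20% loss rate is assumed. The result is that these inputs "would require an estimated sample size of 2,761 patients". From a 2.4% prevalence of ischaemic heart disease the section then concludes that "115,042 health service users will be needed".
- **Study design.** "The design is a quasi-experimental uncontrolled before-and-after study". Ethical aspects confirms that there are no comparison groups and no randomisation.
- **Statistical analysis, 2. Analytical strategy.** The change in percentage controlled "between baseline and the end of the study will be assessed using the McNemar test". Logistic and multilevel logistic models follow, with physician as the cluster.
- **Study sample.** There are 3,402 patients registered up to December 2008, plus patients newly diagnosed in 2009 and 2010. Under Main independent variable, baseline control is the latest 2008 LDL-C value.

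**The concern.** A McNemar test uses each patient twice, once before and once after. Its sample size depends on the share of patients who change status, and it counts patients, not group members. The sample size section gives no discordant share and no within-patient correlation, and its total is about what a two-arm parallel cluster trial would need. If so, the required number, the number of users derived from it and the 90% power all describe a different study.

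Two inputs are also hard to read as printed. A confidence interval of 0.05 attached to a mean cluster size has no clear meaning, and an increase of 10% from 35% may be absolute or relative. A reader who wants to know what change this cohort can detect cannot learn it from the paragraph.

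**Working it through.** **Inputs.** From the sample size section: p1 = 0.35, increase 10%, two-sided alpha 0.05 (z = 1.96), power 90% (z = 1.2816), 25 patients per physician, the value 0.05, and 20% loss. Two readings are inferred: 10% is taken as 10 percentage points (p2 = 0.45), and 0.05 as an intraclass correlation (ICC).

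**Step 1: reproduce 2,761.**
- Two independent proportions, per group: n = [1.96·√(2·0.40·0.60) + 1.2816·√(0.35·0.65 + 0.45·0.55)]² / 0.10² = 502.3.
- Design effect: 1 + (25 − 1)·0.05 = 2.2.
- Total: 2 · 502 · 2.2 / 0.8 = 2,761.0. Rounding up to 503 gives 2,766.5.
- A relative 10% (35% to 38.5%) gives a two-group total of about 21,900, so the absolute reading is the one that fits.

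**Step 2: what the 2,761 counts.** 2,761 / 0.024 = 115,042, the stated number of users. The article therefore treats 2,761 as distinct patients, not as measurements.

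**Step 3: the paired requirement.** Write d = 0.10 and ψ for the discordant share. Then n = [1.96·√ψ + 1.2816·√(ψ − d²)]² / d². With within-patient correlation φ, ψ = 0.35·0.55 + 0.65·0.45 − 2φ·√(0.35·0.65·0.45·0.55) = 0.485 − 0.4746φ. The article gives no φ, so the values below are assumptions. The last three columns keep design effect 2.2 and 20% loss.

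| φ (assumed) | ψ | pairs | × 2.2 / 0.8 | users (/ 0.024) | power with 2,761 enrolled |
|---|---|---|---|---|---|
| 0 | 0.485 | 505 | 1,390 | about 57,900 | 99.6% |
| 0.2 | 0.390 | 406 | 1,116 | 46,500 | 99.9% |
| 0.4 | 0.295 | 306 | 841 | about 35,000 | above 99.9% |

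Power uses 2,761 · 0.8 / 2.2 = 1,004 effective pairs. The ratio 2,761 / 1,390 is 1.99 at φ = 0, and it rises with φ.

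**Step 4: can any McNemar calculation on these inputs give 2,761?** The largest possible discordance for 35% to 45% is 0.35 + 0.45 = 0.80. It needs about 837 pairs, or about 2,300 patients after × 2.2 / 0.8. With design effect 2.2 the answer is no.

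**Step 5: what the available cohort detects.** 3,402 · 0.8 = 2,722 pairs, and 2,722 / 2.2 = 1,237 effective pairs. Solving the formula in step 3 for d at 90% power gives 6.3, 5.7 and 4.9 points at φ = 0, 0.2 and 0.4.

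**The case against.** **The exact formula is inferred.** This stands in part. The figure 2,761.0 needs 502.3 truncated to 502, and a continuity-corrected version also fits (2 · 523 · 2.2 · 1.2 = 2,761.4). Both routes contain the factor 2 for independent groups, so the mismatch remains.

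**The increase may be relative.** For 35% to 38.5%, the paired requirement at design effect 2.2 exceeds 2,761 for correlations up to 0.7, and the direction of the error would reverse. That reading does not reproduce 2,761 by the two-group formula. A McNemar calculation would reach it only with a discordance that the article never states. The ambiguity is a reason to state the scale.

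**The design effect may not carry over.** This stands. In a before-after comparison within the same physicians, the relevant ICC is that of the change, which the article does not give. Sessions are held by centre, so change might cluster there too. As an illustration, at φ = 0 a design effect of 2,761 · 0.8 / 505.4 = 4.37 brings the paired requirement back to 2,761. That is an ICC of change of (4.37 − 1) / 24 = 0.14. A reader might take 1,390 as a ceiling; it is not one.

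**The study is not purely paired.** This is true. Patients newly diagnosed in 2009-2010 have no 2008 baseline and supply no McNemar pairs, and regression models are planned as well. Neither point justifies doubling the number for a second independent group.

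**Nothing is harmed.** This largely stands. The whole register is used, and 3,402 exceeds 2,761 and every paired figure in the table. A reader might infer that the surplus power makes a background trend likely to be declared an effect. That risk comes from the missing control group, which the Discussion already concedes, and correcting the calculation would leave it unchanged.

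**Conclusion.** The stated size, the users needed and the 90% power are not those of the design. They are the figures for two independent groups, applied to one cohort with a paired test. That conclusion rests on reading 10% as percentage points and 0.05 as an ICC, the readings that make the stated inputs yield 2,761.

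The error is conservative under the article's own design effect. The paired requirement is 841 to 1,390 for correlations 0.4 to 0, and power at 2,761 is at least 99.6% for 10 points at any non-negative correlation. The study is not underpowered for its planned effect on these assumptions.

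Two stronger statements are tempting. One is that the number is overstated at least two-fold. At zero correlation the ratio is 1.99, and anything larger needs a positive correlation and the 2.2 design effect, neither of which the article establishes for change. The other is that the cohort detects changes half the planned size. The range is 49% to 63% of 10 points, and only the highest correlation in the table reaches about half.

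This is a reporting correction. No recruitment or test has to change.

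**What to change.** Keep the 3,402 registered patients and rewrite the sample size paragraph:

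1. Call the 0.05 an intraclass correlation, and give the effect as 10 percentage points (35% to 45%).
2. Recompute for paired proportions with a stated discordant share or within-patient correlation and a stated ICC of the change. Show the result as a range over plausible values, not as a maximum.
3. Restate the number of users from the new requirement.
4. Give the change that the available paired cohort detects with 90% power. On design effect 2.2 and 20% loss this is about 4.9 to 6.3 points for correlations 0.4 to 0.
5. Say that patients newly diagnosed in 2009-2010 do not enter the McNemar pairs.

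The cost is one paragraph and a short calculation. No patients are added and the analysis does not change. The ICC of the change and the discordance may have to be assumed if the sponsor has no earlier data, and the paragraph should then say so.

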#### 2. Analytical strategy

The statistical analysis will be preceded by an examination of outliers, data cleaning, identification and labelling of missing and/or unenforceable values, and labelling of variables and variable categories.

Variables will be summarised as the mean and 95% CI for continuous variables, and as absolute values or percentages and 95% CI for categorical variables. Statistical significance will be concluded for values of p < 0.05. The difference in percentage control of LDL-C levels between baseline and the end of the study will be assessed using the McNemar test. To assess the improvement of control of c-LDL an analysis of covariance using logistic regression will be carried out. Subsequently, a multilevel logistic regression model will be developed. The main independent variable in the both models will be "intervention", adjusted for baseline values and potential confounders. Physician will be considered a cluster in the multilevel regression).

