#### Main independent variable

Percentage of patients who achieve a good control of LDL-C, measured in milligrams/decilitre (mg/dl). The control goal for IHD patients is LDL-c < 100 mg/dl.

At the beginning of the study, a patient will be considered to be controlled if the most recent measured level of LDL-C (in 2008) is < 100 mg/dl.

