### Ethical aspects

The presented project has been evaluated by the Clinical Research Ethics Committee of the primary care research institute, IDIAP Jordi Gol, Barcelona June 12, 2009 (Ref: P09/25). Since the project examines specific information about the illness control and the information was obtained anonymously from a population approach (before and after intervention), the Committee did not consider necessary to require the Informed Consent. The intervention was applied to all patients and there were not neither comparative groups nor randomized distribution.

The study guarantees the confidentiality of professionals' data. The data collected and generated will be included in two databases as a data decoupling procedure to adhere to data protection legislation and to maintain individual privacy. For this reason there will be different types of files, each with a different password to be renewed periodically and which shall only be accessible by a responsible person.

The first file will be a demographic database, in which each patient is assigned a unique code. The second file will include the patient codes linked to the main clinical variables relevant to the study that will include the results of the study and the clinical variables for statistical analysis. The databases will remain stored on a hard disk of a PC with a renewable password located in a locked office with controlled access.

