## Discussion

The limitations of the project are that it is a before-and-after intervention study without a control group, randomisation or masking. No control group has been proposed in order to ensure that the educational intervention reaches the maximum number of professionals.

Presential training courses are being undertaken by both physicians in hospitals (cardiologists and internists) and primary care settings, since both groups are responsible for the diagnosis and monitoring of patients with IHD.

In fact, all the 11 PCAs have two referral laboratories for the determination of the LDL-C but both offer the same quality guarantees for this value determination. Another limitation may be that the follow-up period is insufficiently long to detect changes in morbidity and mortality and prescription habits of physicians. However, we hope to detect at least a trend towards an improvement in our results.

Previous studies of the implementation of guidelines do not show very encouraging results regarding the overall improvement of the quality of patient care but do indicate an increase in drug prescription [11,12].

This project is interesting because vascular disease has a high morbidity and mortality. In the Spanish population as a whole, this has been the leading cause of death for many decades. It causes severe disability among the population and is responsible for a substantial increase in healthcare costs.

Statins are the drugs of first choice for the treatment of DL in patients with IHD and have been shown to reduce cardiovascular morbidity and mortality. They are also easy to use and have a good clinical safety profile.

Despite the evidence of the need to achieve a LDL-C level of ≤ 100 mg/dl for patients with IHD, this occurs in only 35% of patients in our area (2008 data). The collaboration between primary care and hospital units with the help of the aforementioned methodology seeks to achieve a degree of control sufficient to decrease morbidity and mortality among these patients, as well as to clear the way for the development of consensual guidelines to unify patient management criteria and significantly improve the health of our population.

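### Both adjusted models estimate an 'intervention' effect with baseline adjustment, but there is no comparison group, so the term is constant or, with stacked before/after rows, mis-specified

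*Protocol article*

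**What the plan says.** Under Analytical strategy, the change in the percentage controlled between baseline and study end is tested by McNemar. For the improvement in control, "an analysis of covariance using logistic regression will be carried out", followed by a multilevel logistic model in which physician is a cluster. "The main independent variable in the both models will be" the term 'intervention', "adjusted for baseline values and potential confounders". The article does not define how that term is coded.

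The rest of the article leaves no untreated patients. Study design: "The design is a quasi-experimental uncontrolled before-and-after study". Ethical aspects: "The intervention was applied to all patients and there were not neither comparative groups nor randomized distribution". Discussion: "it is a before-and-after intervention study without a control group, randomisation or masking".

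The outcome is LDL-C below 100 mg/dl, and baseline status comes from the last 2008 value. Classroom attendance and completion of the voluntary on-line course are also recorded, as measures of physician participation.

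**The concern.** A baseline-adjusted analysis of covariance compares groups at the end of follow-up, given where each patient started. It needs an exposure that differs between patients, and this design has only a contrast over time. The article combines the model form of a controlled study with an exposure that, by its own account, everyone receives.

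The two regressions are the only analyses of the main objective that adjust for confounders, and the multilevel model is the only one that recognises physician clustering. In an uncontrolled study, readers will look to these models. If the main term cannot be fitted, or is fitted in a form that matches no clear target, the adjusted result cannot be interpreted as the effect of implementing the guideline.

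**Working it through.** **Inputs.** Control rate before: 35% (Sample size). Expected rise: 10%, read as 10 points, so 45% after. Stated sample: 2,761, with 25 patients per physician, two-sided alpha 0.05, 90% power and 20% loss (same section). The within-patient correlation of control status (phi) is not given and is assumed between 0 and 0.7.

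**Checking the 10-point reading against the stated sample size.** Two independent proportions, 0.35 and 0.45, with mean 0.40:

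n per group = [1.96 × √(2 × 0.40 × 0.60) + 1.2816 × √(0.35 × 0.65 + 0.45 × 0.55)]² / 0.10² ≈ 503, or 1,006 in total.

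Reading the article's 0.05 as an intraclass correlation, the design effect is 1 + 24 × 0.05 = 2.2. Then 1,006 × 2.2 / 0.80 = 2,767, within 0.2% of 2,761. A relative 10% rise (35% to 38.5%) would need 21,923. So 35% to 45% is the planned effect. This calculation only fixes the effect size; it neither supports nor weakens the point.

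**Reading 1: one end-of-study row per patient.** The columns are intercept (all 1), 'intervention' (all 1) and baseline control. The matrix has rank 2 of 3, so the 'intervention' coefficient has no estimate.

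**Reading 2: before and after rows stacked, 'intervention' = period, baseline control as covariate.** In every before row the covariate is the outcome itself. The marginal odds ratio is (0.45/0.55)/(0.35/0.65) = 1.52. For the matched odds ratio:

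- p11 = 0.35 × 0.45 + phi × √(0.35 × 0.65 × 0.45 × 0.55)
- p10 = 0.35 − p11 and p01 = 0.45 − p11
- matched OR = p01/p10

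At phi 0.4, p11 = 0.252, p10 = 0.098, p01 = 0.198 and the matched OR is 2.02. Logistic fits to the expected cell counts give:

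| phi (assumed) | matched OR | stacked, baseline-adjusted OR | excess |
|---|---|---|---|
| 0 | 1.52 | 1.74 | 14% |
| 0.2 | 1.69 | 1.91 | 13% |
| 0.4 | 2.02 | 2.28 | 12% |
| 0.6 | 2.99 | 3.37 | 12% |
| 0.7 | 4.79 | 5.43 | 13% |

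(Excess computed from unrounded odds ratios.)

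The model does not match the before rows. At phi 0.4 it fits control probabilities of 0.10 and 0.81 where the data are exactly 0 and 1. Adding a period-by-baseline interaction gives complete separation and divergent coefficients.

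*Percentage-point scale.* A logistic model with an intercept and a period term reproduces the observed proportion in each period. At phi 0.4, before: 0.65 × 0.101 + 0.35 × 0.813 = 0.350. The period log odds ratio of 0.823 moves these fitted values to about 0.204 and 0.908, so after: 0.65 × 0.204 + 0.35 × 0.908 = 0.450. The averaged change is the true 10 points.

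*No true change.* At 35% in both periods the expected-count OR is 1.00 at phi 0.2, 0.4 and 0.6. The standard errors are still too small. In 1,500 simulations per setting with 2,209 pairs (2,761 × 0.8), no physician clustering and no patient level in the model:

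| phi (assumed) | true SD of log OR | mean model SE | type I error | McNemar |
|---|---|---|---|---|
| 0.2 | 0.088 | 0.079 | 0.080 | 0.046 |
| 0.4 | 0.096 | 0.088 | 0.071 | 0.049 |
| 0.6 | 0.112 | 0.105 | 0.063 | 0.049 |

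**Reading 3: 'intervention' = attendance or course completion.** The term varies between physicians and can be estimated. But the on-line course is voluntary, so the contrast is self-selected. It bears on the secondary objective about professional profile, not on the before-after change.

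**The case against.** The best defence is Reading 3. The training is aimed at physicians, participation is recorded for each of them, and every patient is linked to a primary care physician. An end-value model adjusted for baseline, with physician as cluster, fits that data structure. The Ethical aspects sentence about all patients explains why consent was waived and does not say how a model term is coded. It stands that this reading is estimable. It does not rescue the main objective, because the article introduces the models to assess improvement in control and never states this definition.

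A second defence is that row layout, coding and random effects are commonly left to an analysis plan, which may exist and is not shown. The article names physician as a cluster without excluding a patient level. *Baseline values* could also mean characteristics other than LDL-C control, although in an analysis of covariance the baseline outcome is the usual sense. This lowers the severity. It does not remove the point: the article itself fixes the exposure term, the baseline adjustment and the model form, and these do not fit a single-group design without redefinition.

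A reader might also set the stacked odds ratios of 1.91 and 2.28 against the marginal 1.52 and infer inflation of 26-50%. That mixes estimands. A covariate-conditional odds ratio normally exceeds a marginal one, and a sound patient-random-intercept model would do so too. The matched odds ratio is the fairer comparison.

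Finally, the article heads the outcome ("Percentage of patients who achieve a good control of LDL-C") as the main independent variable. That is a wording slip and adds no weight here.

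**Conclusion.** The point holds for the adjusted and clustered analyses. Followed as an end-value analysis of covariance, the main term cannot be estimated. Followed with stacked rows and baseline control as covariate, the odds ratio is about 12-14% above the matched one at 35% to 45%, and type I error is about 0.06-0.08 instead of 0.05. These sizes rest on an assumed within-patient correlation, on baseline values including baseline LDL-C control and, for the type I error, on no patient level being added.

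A reader might infer that the adjusted effect is badly distorted on every reading, or that the main objective has no usable test. The documents do not support either. The averaged percentage-point change is unbiased, the odds ratio is 1.00 under no change, the training-exposure reading is estimable, and this point leaves the McNemar comparison of crude paired change intact. Severity: should-fix.

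**What to change.** Reword the Analytical strategy as follows.

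- Define 'intervention' as before/after period, with one row per patient per period and LDL-C control named as the dependent variable.
- Account for both patient pairing and physician clustering: random intercepts for patient and physician, or GEE or cluster-robust standard errors at physician level (which cover the pairing when both rows of a patient sit under one physician).
- Remove baseline LDL-C control as a covariate from this model.
- Report the marginal change in percentage points with its confidence interval, so that the result does not depend on which odds ratio is meant.
- Address professional profile through period-by-trait interactions.
- Keep the baseline-adjusted end-value model only for comparing physicians by training exposure, labelled observational.

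The cost is analysis wording only. No new data are needed.
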